### The randomization process

At the beginning of the trial, the participant will be randomized to either the telemonitoring group or the usual care group during a visit to the endocrinology clinics at Aalborg University Hospital or Nykøbing Falster Hospital. Randomization will be performed in RedCap (2020 Vanderbilt University) based on a computer-generated random list (ratio 1:1). The list will be concealed in RedCap until interventions are assigned. Prior to randomization, the participants will be informed about the trial and sign informed consent. Medical laboratory technicians, nurses, and researchers will enroll the participants, give them information regarding the trial, obtain informed consent, and assign the participants to interventions. The trial is open-labeled, since both participants and staff involved in the trial will know whether the participants are being telemonitored or not.

Basic baseline information about the participants will be obtained at trial start in addition to questionnaire data (Table 1). Moreover, a venous blood sample will be drawn to cover secondary endpoints as well as baseline information. A lab technician/nurse will be responsible for the blood sampling.

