#### End of trial

At end of trial, participants from both groups visit the endocrinology clinic again. The participants are encouraged to answer various questionnaires and a laboratory technician/nurse will take a venous blood sample. The flow of the trial design is illustrated in Fig. 1.

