#### Exploratory endpoints

The exploratory endpoints are based on questionnaires and monitoring data, and include the following:5)Change from baseline in CGM endpoints 3 months after randomization: number of days worn, percentage of time active, mean glucose, glycemic variability, time in hyperglycemia (>13.9 mmol/L), time in hypoglycemia (<3.0 mmol/L), episodes (hypoglycemia and hyperglycemia) 15 min and area under the curve.6)Use of the telemonitoring equipment: The frequency of use of the telemonitoring equipment during the trial is assessed directly from the delivered devices.7)Telemonitoring usability: Data is collected via the Telemedicine Usability Questionnaire. The telemedicine group will answer the questionnaire at the 3-month assessment.8)Diabetes-related quality of life: Between group differences measured by the DIDP questionnaire at baseline and at the 3-month assessment.9)Quality of Life: Between group differences measured by the SF-12 questionnaire at baseline and at the 3-month assessment.10)Adherence to insulin dosing and timing. Any differences in the use of insulin between the two groups are examined based on data from the insulin pens.11)Number of hypoglycemic events 3 months after randomization.

In addition, qualitative interviews will be conducted with selected participants in order to gain deeper insight into the participants’ experience of telemonitoring.

Hospital staff will make appointments with the participants for the final visit, during which the final data will be collected. Should a participant not show up for the appointment, hospital staff will contact the participant by telephone to schedule a new appointment. Participation in the final visit is considered to be completion of trial regardless of the degree of use of technologies. The trial ends after the last participant’s final visit.

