#### Plans for collection, laboratory evaluation, and storage of biological specimens

As described, a blood sample is drawn at the beginning and at the end of the trial for all included subjects. This is initially done for analysis of the following: HbA1c, lipids, c-peptide, and insulin. Approx. 60 ml will be drawn per sample. All samples will be analyzed immediately after extraction at Aalborg University Hospital, after which the samples will be destroyed.

A research biobank is set up to collect material for later analysis of parameters, which were not possible to predict before the start of the trial. This specifically includes cardiovascular risk and bone disease associated with glucose variation. These factors include:P1NPCTXSclerostinGlucagonPlasma-ionized calciumPlasma albumin-adjusted calcium

All blood samples will be taken and handled by lab technicians/nurses at SDCN or SDCS during the initial and final visit. All biological material is destroyed at the end of the project when all analyses related to the specific research project have been completed.

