### Statistical analysis

Sample size calculation is based on the following formula:$$n=\frac{2{\sigma_d}^2}{\tau^2}{\left({z}_{a/2}+{z}_{\beta}\right)}^2$$

*τ* is the minimum detectable difference in mean and *σ*_*d*_ is the standard deviation of the difference. Based on an assumed difference in reduction of CGM time in the range of 80 min (*τ* =  − 80), a standard deviation of the difference of 220 min (*σ*_*d*_ = 220) [34], a significance level of 0.05 and a power of 0.9, the number of participants is 320. With an estimated dropout rate of 25%, 400 participants must be included. The large dropout rate is primarily expected in the usual care group. To minimize loss to follow-up, the trial staff will provide the participant in the usual care group with a printout of their data at study completion and offer a consultation regarding the data.

A variety of statistical methods will be applied to investigate the objectives of the trial after end of trial. No analysis is planned during the data collection period. All statistical methods will be applied on the Full Analysis Set that includes all randomized participants. Imputation of missing data is described below.

Change in CGM metrics and total daily insulin dose will be calculated as the difference between mean of the metric, e.g. time in range, or total daily insulin dose the 2 weeks before end of trial and the 2 weeks after randomization. Using data from all patients, the primary endpoint will be investigated with the following primary analysis. The primary analysis is performed with a statistical model that includes multiple imputation, where patients without CGM at scheduled visits get their CGM time in range imputed. An analysis of variance model with the region as a factor and CGM time in range at baseline as a covariate is used to estimate the effect of telemonitoring on CGM time in range. Sensitivity analysis with similar configurations will be applied to subgroups.

The secondary endpoints will be investigated using statistics, models, and algorithms that include differential equations in compartment modeling, as well as algorithms in Machine Learning.

All participants included in the trial will be included in the statistical analyzes. The statistical significance level of 5% is used in the trial (*p* < 0.05). Participation in the final visit is considered to be completion of trial regardless of the degree of use of technologies. The trial ends after the last participant's final visit.

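### Entry HbA1c should join region and baseline time in range in the primary model, and HbA1c from both visits should be prespecified for imputing missing time in range

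*Protocol article*

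**What the plan says.** All references are to the protocol article. The Statistical analysis section announces that imputation will be described and then says two things in separate sentences. First, the primary analysis "includes multiple imputation, where patients without CGM at scheduled visits get their CGM time in range imputed". Second, the treatment effect is estimated with "An analysis of variance model with the region as a factor and CGM time in range at baseline as a covariate". No imputation predictors are listed, and no variable is ruled out.

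The same section defines change in time in range as the mean over the last two weeks of the trial minus the mean over the two weeks following randomization. It plans for 25% dropout and expects most of it in usual care.

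On blood sampling, the section on biological specimens says that "a blood sample is drawn at the beginning and at the end of the trial for all included subjects", with HbA1c among the analytes, and that "All blood samples will be taken and handled by lab technicians/nurses at SDCN or SDCS during the initial and final visit". The section on the randomization process confirms the entry sample: "a venous blood sample will be drawn to cover secondary endpoints as well as baseline information".

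On completion, the Exploratory endpoints section says: "Participation in the final visit is considered to be completion of trial regardless of the degree of use of technologies".

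**The concern.** The two variables named for the primary analysis are weakest for the participants whose outcome is missing.

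- **Early leavers.** Baseline time in range is collected after randomization. A participant who leaves in the first days has neither a baseline nor a final value. Of the two named variables only region is left, although entry HbA1c was measured.
- **Attenders without CGM.** The completion rule allows a participant to finish without usable CGM in the last two weeks. Usual care wears the sensor only in the first and last 20±2 days, so a missed final window leaves no nearby CGM data. The 3-month HbA1c of these participants is direct evidence on their glycaemia.
- **Timing of baseline.** During the baseline window the telemonitoring arm already has its unblinded devices and has its one-week call (The telemonitoring group). Entry HbA1c is free of that influence.

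What is at stake is the primary contrast. If missingness is unequal between arms and related to glycaemia, an imputation that ignores available glycaemic data treats the missing participants as typical of their arm.

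**Working it through.** **Inputs from the protocol article.** Difference 80 min, SD 220 min, significance level 0.05 with z for α/2, power 0.90, 320 participants, 25% dropout, 400 randomized 1:1.

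**Assumptions (not in the documents).** r is the correlation of 3-month HbA1c with final time in range, given baseline time in range. a is the share of participants missing final time in range who still have a 3-month HbA1c.

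**1. The plan's own figure.** n per arm = 2 × 220² / 80² × (1.960 + 1.282)² = 15.125 × 10.51 ≈ 158.9, so 159 per arm and 318 in total. The stated 320 is reproduced. The 400 is 320 × 1.25. Losing 25% of 400 leaves 300.

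**2. What each type of participant provides.**

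| Participant | Baseline time in range | Final time in range | Entry HbA1c | 3-month HbA1c |
|---|---|---|---|---|
| Leaves in the first days | no | no | yes | no |
| Leaves later | yes | no | yes | no |
| Attends final visit, no usable final CGM | normally yes | no | yes | yes |
| Attends with CGM | yes | yes | yes | yes |

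Entry HbA1c is available in every row. The 3-month value helps only in the third row, and the documents do not say how many participants fall there.

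**3. Precision gained from 3-month HbA1c.** Take 300 participants with final time in range and 100 without. The variance of the contrast when HbA1c is used efficiently is

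V = 4 × 220² × [(1 − r²)/300 + r²/(300 + 100a)].

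- a = 0: V = 193,600 / 300 = 645.3, SE 25.40 min, power Φ(80/25.40 − 1.960) = 88.3%.
- r = 0.7, a = 0.5: V = 193,600 × (0.51/300 + 0.49/350) = 600.2, SE 24.50 min, power 90.4%.
- r = 0.7, a = 1: V = 193,600 × (0.51/300 + 0.49/400) = 566.3, SE 23.80 min, power 91.9%.

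| Power | a = 0 | a = 0.5 | a = 1 |
|---|---|---|---|
| r = 0.3 | 88.3% | 88.7% | 89.0% |
| r = 0.5 | 88.3% | 89.4% | 90.2% |
| r = 0.7 | 88.3% | 90.4% | 91.9% |

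Before rounding, the largest gain in this table is 91.95 − 88.28 ≈ 3.7 points.

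**4. Bias, by large-sample simulation.** Further assumptions: true effect 80 min; residual SD 220 min; 37% missing in usual care and 11% in telemonitoring (74 + 22 = 96 of 400, or 24%); log-odds of missingness rising by 0.5 per SD of worse final glycaemia; imputation by regression within arm.

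- Without HbA1c, the estimate is about 53 min, a bias of 80 − 53 = 27 min.
- r = 0.7, a = 0.5: about 60 min, so 7 of the 27 min are recovered.
- r = 0.7, a = 1: about 66 min, so 13 of the 27 min are recovered.
- Over r from 0.5 to 0.8, the estimate is roughly 56 to 62 min at a = 0.5 and 59 to 70 min at a = 1.
- a = 0: about 53 min, with nothing recovered.

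No figure was computed for entry HbA1c. The documents give neither the number of early leavers nor the correlation of entry HbA1c with final time in range beyond baseline time in range.

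**The case against.** A reader might infer that the plan imputes time in range without HbA1c. The text does not support that. The sentence naming region and baseline time in range describes the model that estimates the treatment effect. Imputation has its own sentence, which names no predictors, and an imputation model may hold auxiliary variables that the analysis model omits. An article also commonly leaves the predictor list to a full protocol or SAP, so the missing list is not itself a fault.

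A reader might also infer that 25% of time-in-range values will be missing and that HbA1c can fill them in. The 25% is a planning dropout rate. Under the completion rule, a dropout is someone who does not attend the final visit, and that person has no final blood sample either. For them a = 0, and 3-month HbA1c adds nothing.

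Further objections are that the bias figures rest on an assumed mechanism in which missingness depends on the unseen outcome, and that most of the bias remains in any case (20 of 27 min at r = 0.7, a = 0.5). Omitting a second baseline covariate is also not an error when the baseline of the outcome is already in the model.

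All of this stands, and it limits the point to an improvement. It does not remove the point. Entry HbA1c needs no final visit, so the argument about dropouts does not touch it. Baseline time in range is collected after randomization and can be absent. Adjusting the treatment effect for 3-month HbA1c would be wrong, because it is a post-randomization outcome, but using it only to impute does not do that.

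**Conclusion.** The point holds as a modest, low-cost improvement to the stated primary analysis. The documents contain no error or contradiction here, and they do not show that HbA1c is left out of the imputation.

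The case for entry HbA1c rests on the documents alone: it is planned for everyone, at trial start, and survives early dropout. Its numerical benefit is not quantified.

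The benefit of 3-month HbA1c depends on how many participants attend the final visit without usable CGM. It runs from none, if all those missing CGM are non-attenders, to about 13 of 27 min of bias and at most about 3.7 points of power, if all of them attend and r = 0.7. Both ends rest on the assumptions listed in the working. HbA1c does not remove the remaining bias under that missingness mechanism.

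**What to change.** 1. Add entry HbA1c as a covariate beside region and baseline time in range in the primary model.
2. Prespecify multiple imputation of time in range separately by arm, with region, entry HbA1c, 3-month HbA1c and any available time in range as predictors. State that 3-month HbA1c is used for imputation only and never as a covariate in the analysis model.
3. Fix the predictor list before data are analysed, because the Trial design section says that the analysts are not blinded to group. If the SAP or full protocol already does this, only step 1 remains.

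The cost is a sentence or two. The samples are already planned in both arms at both visits. The downside is a slightly larger imputation model.

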### Monitoring

#### Composition of the coordinating centre and trial steering committee

The steering committee of the ADAPT-T2D consortium will oversee the trial and serve as the data monitoring committee. Furthermore, a research lab technician from Aalborg University Hospital, who are not directly involved in the trial, will perform audit on the data quality throughout the trial period.

The core group running the trial will consist of lab technicians and a research project manager. Besides continuous meetings throughout the trial period (when necessary), the core group will have monthly status meetings. The primary investigator, the data auditing lab technician, and other relevant project members will also be invited to these meetings and attend when relevant.

#### Adverse event reporting

There are no expected harms related to the trial. Any unexpected adverse events related to the trial are recorded in the electronic patient journal and in the trial master file in RedCap with information on whether the primary investigator attributes association to the trial. All adverse advents associated to the trial will be reported in the primary trial publication.

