#### The usual care group

The usual care group will receive standard of care in accordance with Danish guidelines. In addition, a new Novo Nordisk insulin smart pen is provided to all participants in the usual care group. The smart pen will be used for long-acting insulin for all participants. A second smart pen will be provided to those participants who are also on short-acting insulin. The pens received by the usual care group will be blinded to ensure that participants are unable to see their data. The pens will collect data used for later analysis and comparison of adherence to insulin prescription in the intervention group and the control group. In addition, the usual care group will be provided with a continuous glucose monitor (CGM), which they will be asked to wear the first and last 20±2 days of the trial period. The CGM will also be blinded so that the participants are unable to see their data. The CGM data will be used for analysis of the primary and secondary outcomes. Thus, participants in the usual care group will receive usual care with an addition of the blinded devices. No changes in treatment, including medicine/dosage, will be performed based on the blinded devices, as neither patients nor clinical staff will have access to the data. The control group will not be compensated financially for their participation in the trial. However, by the end of trial, the monitoring lab technicians/nurses will offer to print out the data from the blinded devices and go through them with the participants in the usual care group.

The authors hypothesize that the telemonitoring intervention will significantly improve time-in-range compared to usual care.

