#### Criteria for discontinuing

The trial will be terminated in the event of any serious adverse events related to the trial as considered by the primary investigator. The trial is stopped for each participant if severe hypoglycemia, ketoacidosis, or severe hyperglycemia is recorded and related to the trial based on the primary investigator’s assessment.

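### Adverse events are filtered on an open-label judgement of relatedness to the trial, so reported counts cannot be compared fairly between arms

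*Protocol article*

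**What the plan says.** The Protocol article sets the rule under Adverse event reporting: "There are no expected harms related to the trial. Any unexpected adverse events related to the trial are recorded". These records are kept in the patient's journal and in REDCap. A further clause adds that each one comes "with information on whether the primary investigator attributes association to the trial". What the primary paper will contain is fixed in a separate sentence: "All adverse advents associated to the trial will be reported in the primary trial publication".

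Under Criteria for discontinuing, participation stops "if severe hypoglycemia, ketoacidosis, or severe hyperglycemia is recorded and related to the trial based on the primary investigator’s assessment". The whole trial ends if a serious adverse event is considered related to it, again in the primary investigator's view.

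On the arms, The usual care group says: "No changes in treatment, including medicine/dosage, will be performed based on the blinded devices". The telemonitoring group describes at least three scheduled calls, further calls when staff see unusual data, and possible insulin dose changes after a doctor is consulted. Trial design and The randomization process both say that the trial is open-label.

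**The concern.** A randomized comparison of harm is protected from bias when events are counted in each arm by the same rule, without regard to what anyone believes caused them. Here an event must first be judged related to the trial, by someone who can know the arm. In telemonitoring there is a ready causal path: staff watched the data, gave advice and may have changed a dose. In usual care that path does not exist, so the same clinical event has less reason to be called trial-related.

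What is at stake is the published harm table. The Discussion offers the trial as a possible basis for national implementation. A table filtered in this way could show an excess of severe events in the telemonitoring arm where none exists, or hide a real reduction.

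**Working it through.** **Step 1: what the filter covers.** The recording sentence names events that are both unexpected and related. Its natural reading is that other events are not recorded. The clause that follows stores whether the investigator attributes association, which would serve no purpose if every recorded event were already related. The recording rule is therefore unclear. The publication sentence is not: it commits only to associated events. So the filter reaches the published table on either reading of the recording sentence.

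**Step 2: expectedness.** Adverse event reporting declares no expected harms. Criteria for discontinuing names three severe glycaemic events in advance. If these count as expected, the word unexpected removes them from the recording rule. If they do not, they are recorded only when judged related. The article does not say which applies.

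**Step 3: routes to a related judgement, by arm.**

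| Route | Telemonitoring | Usual care |
|---|---|---|
| Calls and advice based on monitored data | Yes | No |
| Dose changes based on monitored data | Possible | No |
| Switch of insulin brand at trial start (Eligibility criteria) | If needed | If needed |
| Study insulin pen | Yes | Yes, blinded |

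Two routes are shared and two exist in one arm only. This gives the direction of the bias.

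**Step 4: harm data outside the filter.** Secondary endpoints include time below and time above range. Exploratory endpoints include time below 3.0 mmol/L, time above 13.9 mmol/L, CGM episodes and a number of hypoglycaemic events. None carries a relatedness condition. Statistical analysis computes change in CGM metrics from the two weeks after randomization and the two weeks before trial end, and both arms wear CGM in those windows.

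Usual-care coverage over the whole trial is 2 × (20 ± 2) = 36 to 44 days. The article gives the length only as 3 months, so I assume 84 to 92 days:
- lowest: 36 / 92 = 39%
- middle: 40 / 90 = 44%
- highest: 44 / 84 = 52%

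Telemonitoring wears CGM throughout. If the hypoglycaemic event count is taken from CGM over 3 months, observation time is unequal. The article states neither its source nor its definition.

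**Step 5: illustration of size (assumed values).** Events counted in an arm = n × r × q, where n is participants, r the true 3-month risk and q the share judged related. From the article, n = 400 / 2 = 200. Assume the same risk in both arms, r = 1% to 5%, with q = 5% to 10% in usual care and 50% to 90% in telemonitoring.
- True events per arm: 200 × 0.01 = 2 to 200 × 0.05 = 10.
- Counted, usual care: 200 × 0.01 × 0.05 = 0.1 to 200 × 0.05 × 0.10 = 1.0.
- Counted, telemonitoring: 200 × 0.01 × 0.50 = 1 to 200 × 0.05 × 0.90 = 9.

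In general, the reported risk ratio (telemonitoring to usual care) equals the true ratio multiplied by q(telemonitoring) / q(usual care). Equal shares give no distortion. If telemonitoring truly halved the risk, the reported direction would reverse once its share exceeded twice the usual-care share.

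**The case against.** **Harm is measured elsewhere.** A reader might infer that the trial cannot compare harm between arms at all. The article does not support that. The endpoints in Step 4 are unfiltered and cover glucose-based harm, which is a main safety question here. This objection stands and limits the point to reported adverse events. It does not remove the point: CGM shows glucose values, not whether an event was clinically severe, and it cannot identify ketoacidosis or other serious events.

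**Usual-care events can be trial-related.** A reader might also infer that severe hypoglycaemia in usual care would almost never be counted. That goes too far. The insulin switch at trial start can reach either arm and is a direct route to a related event. The number of hypoglycaemic events may also capture severe ones, since its source is not stated. Under-counting is likely; near-total loss is not shown.

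**Recording may come first and attribution second.** The attribution clause, and the discontinuation text "severe hypoglycemia, ketoacidosis, or severe hyperglycemia is recorded and related to the trial based on the primary investigator’s assessment", can be read that way. The doubt is fair for recording. It does not touch the publication commitment.

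**Naming a stopping event does not make it expected.** This is a reasonable reading, so the two sections conflict less sharply than they first appear to. They still leave open how those events are classified and recorded.

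**The article condenses a fuller protocol.** How events are sought may be set out there, and its absence here is no fault. The recording and publication rule, however, is stated in the article.

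**Conclusion.** The point holds for reported adverse events. As written, publication is limited to events judged related to the trial, and recording is too on its natural reading. The judgement is unblinded, and only one arm has monitoring-driven contact and dose changes. Reported severe hypoglycaemia, ketoacidosis, severe hyperglycaemia and other serious events therefore cannot be compared fairly, and usual-care events are likely to be under-counted.

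The direction rests on one assumption: that an investigator who knows the arm will more readily attribute an event where the trial's own monitoring and dose changes were involved. The size is unknown. The counts of 0.1 to 1.0 against 1 to 9 follow only from the assumed risks and shares. CGM comparisons in the shared windows are not affected by this filter.

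**What to change.** - In both arms, record all serious adverse events and all severe hypoglycaemia, ketoacidosis and severe hyperglycaemia, whatever their expectedness or relatedness.
- Find them in the same way in each arm, with one question at the existing final visit and a check of the patient journal.
- Publish counts by randomized arm, with the investigator's relatedness judgement as an added column and not as a condition for entry.
- Reconcile the no-expected-harms statement and the recording wording under Adverse event reporting with the events named under Criteria for discontinuing.
- Reconcile the same wording with the hypoglycaemic event count under Exploratory endpoints, stating that count's definition, source and observation window.

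This changes recording and reporting only, not clinical management. The cost is a few extra REDCap fields, a journal check per participant and a slightly longer harm table.
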